### Procedure for unblinding if needed {17b}

Not applicable. This study is on simple blinding: physicians do not know the group while coaches and patients are unblinded.

## Data collection and management

### Plans for assessment and collection of outcomes {18a}

All questionnaires except the GPAC and CGIC are self-administered questionnaires completed by the patient either on paper or directly on a patient secure access to the eCRF. Instructions are given to the patient to complete each questionnaire.

The Fibromyalgia Impact Questionnaire (FIQ) is composed of 10 questions. The first question contains 11 items related to the ability to perform large muscle tasks - each question is rated on a 4-point Likert-type scale. Items 2 and 3 ask the patient to mark the number of days they felt well and the number of days they were unable to work (including housework) because of fibromyalgia symptoms. Items 4 through 10 are horizontal linear scales on which the patient rates work difficulty, pain, fatigue, morning tiredness, stiffness, anxiety, and depression. The French version has been validated by Perrot et al. [30].

The Pittsburg Sleep Quality Index questionnaire is a 19-item, self-rated questionnaire designed to measure sleep quality and disturbance over the past month in clinical populations. The 19 items are grouped into 7 components, including (1) sleep duration, (2) sleep disturbance, (3) sleep latency, (4) daytime dysfunction due to sleepiness, (5) sleep efficiency, (6) overall sleep quality, and (7) sleep medication use. Each of the sleep components yields a score ranging from 0 to 3, with 3 indicating the greatest dysfunction. The sleep component scores are summed to yield a total score ranging from 0 to 21 with the higher total score (referred to as the global score) indicating worse sleep quality. In distinguishing between good and poor sleepers, a global PSQI score > 5 yields a sensitivity of 89.6% and a specificity of 86.5% [31].

The score of the VAS is a real number between 0 and 10. The higher score (10) means the worse pain.

The HAD is an instrument for detecting anxiety and depressive disorders. It was validated and adapted in French [32]. This scale has 14 items rated from 0 to 3 and covers two dimensions. Seven questions are related to the anxiety dimension and seven are related to the depressive dimension, yielding two scores: A (anxiety) and D (depression). The maximum score for each dimension is 21. A score of 11 or higher indicates the probable presence of the disorder.

The Multidimentional Fatigue Inventory is a 20-item scale designed to evaluate five dimensions of fatigue: general fatigue, physical fatigue, reduced motivation, reduced activity, and mental fatigue. The score of each dimension is between 4 and 20. Higher score correspond with more acute levels of fatigue [33].

The EQ-5D-5L is a standardized instrument developed by the Euroquol Group as a measure of health-related quality of life. The EQ-5D-5L contains 5 questions (5Q) on mobility, self-care, usual activities, pain/discomfort, and anxiety/depression with responses rated in 5 levels (5L) and a visual analog scale between 0 and 100. Responses of the 5 questions result to an index [34].

The Global Physical Activity Questionnaire (GPAC) is a questionnaire for the adult population constituted of 16 questions that measure physical and sports activities during a typical week [35]. It aims to collect information on the practice of physical activities (frequency, duration, and intensity of activities) and on sedentary behaviors. The questionnaire covers the following topics: activities at work, during transport, and leisure activities. The results provide a score to classify individuals according to 3 levels of physical activity: low, medium, and high.

The Patient Global Impression of Change and the Clinician Global Impression of Change scales are a 7-point scale depicting a patient's rating of overall improvement [36].

The modular evaluation of key Components of User Experience questionnaire (meCUE) includes 30 items divided into four independent modules: product perception, emotions, consequence of use, and global evaluation. For modules 1 to 3, the user indicates their level of agreement with statements on a 7-point Likert scale, from “strongly disagree” to “strongly agree.” The last question of the meCUE (module 4) asks the user to give an overall evaluation of the product on a scale from − 5 (bad) to + 5 (good) [37].

The solution satisfaction questionnaire (questionnaire created by the sponsor) is a specific questionnaire to the solution including three parts in order to evaluate the patient's satisfaction with the wristband, the mobile application, and the coaching program. A global score between 0 and 100 is given for each part and qualitative questions allow us to better understand this global score.

### Plans to promote participant retention and complete follow-up {18b}

The primary endpoint is collected by a self-questionnaire at D0 and M3. This questionnaire can be completed by the patient directly on the eCRF. Thus, if the patient is unable to attend the follow-up consultation, it will be easy to collect this endpoint. Because of the impact of their symptoms on their quality of life, fibromyalgia patients are generally waiting for a consultation with a physician at the pain center. Thus, we expect very few patients lost to follow-up.

### Data management {19}

Data are collected in an eCRF by the investigating team of each center. The patient can also have a secure access to this eCRF to complete his follow-up booklet at the end of each week and the follow-up questionnaire. This eCRF tool has a data control system to identify data consistency errors, missing data or outliers as soon as they are entered. The data manager also has specific access to request corrections from the investigating team in case of erroneous or missing data. The eCRF includes an audit trail that allows to know for each variable the identity of the person who entered or modified a data as well as the date and time of these actions.

### Confidentiality {27}

In the eCRF, patients are identified by a code composed of the first initial of the surname and first name and the inclusion number in each center. A nominal list linking the patient’s identity to this eCRF identifier is kept in the center by the principal investigator. The data from the wristbands are also non-nominal. When the Fibrepik mobile application is installed, a unique identifier is given to the patient. It is composed of the center number and the patient's inclusion number in the center.

### Plans for collection, laboratory evaluation, and storage of biological specimens for genetic or molecular analysis in this trial/future use {33}

Not applicable. They are no biological specimen collected in this trial.

## Statistical methods

### Statistical methods for primary and secondary outcomes {20a}

Descriptive analyses will be expressed by means − standard deviations and medians − interquartiles for quantitative data, as well as numbers and percentages for qualitative data.

The analysis of the primary endpoint will be performed using a Fisher exact test. For secondary endpoints at M3, all endpoints evaluating a change in score between D0 and M3 will be analyzed via bivariate linear regressions, considering the randomization group and the value of the score at D0. Qualitative criteria will be analyzed using a Fisher test. The secondary endpoint 8 is descriptive and will follow indications for descriptive analysis. For secondary endpoint 9, since analysis considers several measurement points with different states, mixed regressions (linear or logistic depending on the type of variable) will be implemented. Data at M6 from the delayed intervention group will be analyzed for comparison at M3 via a McNemars test (test of proportions for paired data).

These analyses are planned in two stages: (i) all criteria evaluated at 3 months will be performed when all patients have made their follow-up visit at M3 and (ii) all criteria evaluated at 6 and 9 months will be analyzed when the follow-ups at M9 of all patients are completed.

The results will be presented in accordance with the recommendations of the CONSORT Statement. These analyses will be implemented after a consistency check and a freeze of the database, in accordance with the good practices of the Grenoble Alps University Hospital. The software used will be Stata 15 or a more recent version (StataCorp LLC).

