### Trial design {8}

This multicenter superiority trial is randomized into two parallel groups of the type of “Immediate solution” versus “Delayed solution.” The main interest in that design is to limit the disappointment bias, each group has access to the solution: one immediately on the day of randomization, the second group after 3 months, once the primary objective is assessed. The allocation ratio between the two groups is 1:1.

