### Sample size {14}

Considering an alpha risk of 5% and a beta risk of 10%, and assumptions of a rate of patients with a clinically relevant decrease in FIQ of 50% in the Immediate solution group, versus 25% in the Delayed solution group, the number of subjects needed for a comparison of proportions is 77 per group (154 in total). Considering a 10% risk of loss to follow-up, the number of 85 patients per group will be retained (170 patients in total). The clinically relevant decline retained is 14% on the FIQ scale [29].

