## Assignment of interventions: allocation

### Sequence generation {16a}

The randomization list includes random blocks of two different sizes. The block sizes were chosen to be small, to prevent group imbalance in the case of an early interruption of the study. The randomization is stratified by center and on the two levels of fibromyalgia severity assessed by the score on the FIQ questionnaire at inclusion day: moderate form (i.e 39 ≤ FIQ score < 59) or severe form (FIQ score ≥ 59) [29].

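### The primary test ignores the centre and FIQ-severity strata used at randomisation; it is valid but conservative, and a stratified test would recover a modest amount of power

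*Protocol article*

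**What the plan says.** Sequence generation {16a}: "The randomization is stratified by center and on the two levels of fibromyalgia severity assessed by the score on the FIQ questionnaire" at inclusion, with the two levels split at a FIQ score of 59. The Abstract and Study setting {9} give eight centres.

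Statistical methods {20a} names the primary test in one sentence: "The analysis of the primary endpoint will be performed using a Fisher exact test". It mentions no stratum and no covariate. Changes in secondary scores at M3 are analysed by linear regression "considering the randomization group and the value of the score at D0", so each score is adjusted for its own baseline but not for centre or FIQ severity.

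The section on additional analyses {20b} uses centre and severity as subgroup factors. That examines whether the effect varies between strata; it does not adjust the main comparison. The article describes no stratified or adjusted analysis of the primary endpoint.

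Sample size {14} assumes "50% in the Immediate solution group, versus 25% in the Delayed solution group", with 5% alpha, 90% power, 77 evaluable and 85 randomised patients per group.

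**The concern.** When randomisation balances the arms within strata and those strata predict outcome, the difference between arms varies less from trial to trial than an unstratified analysis assumes. The unstratified test is then conservative. Fisher's exact test is conservative in its own right, because it conditions on the total number of responders. Both effects act in the same direction: true size below 5% and power below what the design could deliver.

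Baseline FIQ is a plausible predictor here. It defines the severity stratum and is also the base of the 14% response criterion. At stake is efficiency in a trial planned for 90% power, not the validity of a positive result.

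**Working it through.** **Inputs.** Rates 50% and 25%, alpha 5%, power 90%, 77 per group (Sample size {14}); 1:1 allocation (Trial design {8}); 8 centres × 2 severity levels = 16 strata, so 154/16 ≈ 9.6 evaluable patients per stratum. The sidedness of alpha is not stated; two-sided reproduces the plan's figure.

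**1. The plan's sample size.** Uncorrected two-proportion formula, pooled rate 0.375:

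n = [1.960·√(2·0.375·0.625) + 1.282·√(0.5·0.5 + 0.25·0.75)]² / 0.25² = [1.342 + 0.848]² / 0.0625 ≈ 76.7, hence 77 per group. It reproduces. This formula corresponds to a chi-square test.

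**2. Exact behaviour of the planned test.** Sum Bin(a; n₁, p₁)·Bin(b; n₂, p₂) over all tables (a, b) with a two-sided Fisher p-value ≤ 0.05.

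| Evaluable per group | Fisher power | Fisher size, common rate 25% | Chi-square power |
|---|---|---|---|
| 77 / 77 | 87.6% | 3.3% | 90.6% |
| 85 / 85 | 90.1% | 3.4% | 92.6% |

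At 77 per group, Fisher's size is 3.3%, 3.6% and 3.0% at common rates of 25%, 37.5% and 50%. Fisher first reaches 90% power at 85 per group, which is the randomised number before the expected 10% loss. The figures move with discreteness: with 153 evaluable patients (170 × 0.9) split 76/77, Fisher's power is 88.5–89.3% and its size 3.6–4.4%.

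**3. Stratified test.** Mantel-Haenszel statistic over strata k, with aₖ the Immediate responders, rₖ all responders, n₁ₖ and n₀ₖ the arm sizes, and nₖ their sum:

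X² = [Σ(aₖ − n₁ₖrₖ/nₖ)]² / Σ[n₁ₖn₀ₖrₖ(nₖ − rₖ) / (nₖ²(nₖ − 1))], compared with 1.96².

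Simulation at 77 per group, 16 strata, permuted blocks of 2 and 4 (block sizes assumed), 1,500–3,000 trials per scenario. Prognostic strengths are assumptions.

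| Severity OR / centre log-odds SD / extra baseline slope per SD | Fisher | Chi-square | MH, 16 strata | MH − Fisher | MH − chi-square |
|---|---|---|---|---|---|
| 1 / 0 / 0 | 88.0% | 89.8% | 89.1% | +1.1 | −0.7 |
| 1.5 / 0.3 / 0 | 88.9% | 90.9% | 90.8% | +1.9 | −0.1 |
| 2 / 0.5 / 0 | 89.1% | 91.0% | 92.1% | +3.0 | +1.1 |
| 3 / 0.5 / 0 | 90.1% | 91.2% | 93.0% | +2.9 | +1.8 |
| 2 / 0.5 / 0.5 | 87.9% | 89.9% | 91.1% | +3.2 | +1.2 |
| 3 / 0.8 / 0.8 | 89.5% | 91.2% | 92.6% | +3.1 | +1.4 |

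At a common rate of 25%, size was 2.8–4.2% for Fisher and 4.5–5.8% for Mantel-Haenszel. The Monte Carlo standard error of a power near 90% is √(0.9·0.1/3000) ≈ 0.5 points (0.8 at 1,500 trials).

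The last column separates the two sources. With weak or no stratum effects, the whole gain over Fisher comes from leaving Fisher's conservatism behind. Stratification itself adds about 1 to 2 points once the strata are moderately or strongly prognostic.

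Other simulations assumed severity log-odds of 1.0 and 1.5 (odds ratios e¹·⁰ ≈ 2.7 and e¹·⁵ ≈ 4.5) with centre SDs of 0.4 and 0.6. One implementation gave gains over Fisher of 2.6 and 3.5 points, another about 3.5 to 6 points.

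**4. Standard error.** The unadjusted standard error of the risk difference averaged 0.0749. The actual sampling SD ran from 0.0759 (no stratum effect) to 0.0707 (severity OR 3): no overstatement in the first case, and 0.0749/0.0707 ≈ 1.06, about 6% too wide, in the second.

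**The case against.** The strongest defence is that Fisher's test is valid, simple and errs on the safe side. The shortfall at 77 per group is mainly a mismatch between the sample size formula and the test, and a plain chi-square test would close most of it. That stands, and it limits the size of the point.

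Four stronger readings are tempting, and the article does not support them:

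- **That confidence intervals will be too wide.** This follows only if centre or severity predicts response, which the article does not quantify, and it specifies no interval for the primary endpoint.
- **That the plan fails by giving no effect size with an interval.** A protocol article may leave this to the analysis plan, and {20a} commits to CONSORT reporting.
- **That centre must be adjusted for because each centre's own staff coach.** Until M3 only the Immediate group is coached. A coach effect is therefore a one-arm effect, not a prognostic factor balanced across arms, and stratifying by centre would not recover power from it.
- **That a logistic model with a standardised risk difference is interchangeable with Mantel-Haenszel.** With model-based standard errors, its type I error ran at 6–7% in the simulations.

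Timing is also a fair objection. Inclusions ended on 1 April 2022, so the last M3 window (three months plus two weeks) closed around 15 July 2022, before publication on 5 September 2022. The M3 analysis is due once those visits are complete. Changing a primary test at that stage is more than a wording edit.

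**Conclusion.** The point holds as one of efficiency. The randomisation factors play no part in the primary comparison, and the chosen test is conservative: exact power 87.6% and size about 3.3% at 77 per group, figures that need no assumption about the strata. Stratifying by the randomisation factors keeps size near 5% and gains roughly 1 to 3 points of power over Fisher, possibly more if the strata are strongly prognostic. The size of that gain depends on assumed prognostic strength, and part of it is Fisher's conservatism rather than the omitted strata. There is no added risk of a false positive, and a significant Fisher result would stand.

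**What to change.** - Make the primary analysis a Mantel-Haenszel test with a common risk difference and 95% CI, stratified by centre and FIQ severity. Keep Fisher's exact test as a sensitivity analysis.
- Fix in advance a rule for pooling very small centres, since strata average fewer than 10 evaluable patients.
- If a logistic model with a standardised risk difference is preferred, specify a robust or small-sample variance.
- Add centre and FIQ severity to the M3 linear models.
- Date and document the change before anyone has access to outcome data by arm. If that cannot be shown, leave Fisher as primary and report the stratified analysis as supplementary.

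No new data are needed: the centre is known and the FIQ score is entered in the eCRF before randomisation. The cost is an amendment to the analysis text and evidence of when it was made.

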### Interim analyses {21b}

Not applicable. There are no interim analyses planned.

### Methods for additional analyses (e.g., subgroup analyses) {20b}

A subgroup analysis according to stratification criteria “center” and “severity of disease” will be performed.

### Methods in analysis to handle protocol non-adherence and any statistical methods to handle missing data {20c}

All analyses will be performed in Intention-To-Treat. In addition to this analysis, a per-protocol analysis will be performed by keeping only patients who have been compliant with the treatment. We consider that a patient is compliant if during the first 3 months of solution use, we observe at least 80% of days with two or more sessions per day. This number of sessions is an extract of the wristband log file.

Missing data within the FIQ questionnaire will be accounted for following the recommendations of the scale authors [38]. A sensitivity analysis of the primary endpoint will be performed by imputing missing data not managed via the FIQ use recommendations via multiple imputation if these missing data represent between 5 and 20% of the total data.

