#### Delayed solution description

The “Delayed solution” group consists of (i) from D0 to M3—3 months with the standard of care, *ii) from M3 to M6—3 months with the solution add to the standard of care, and (iii) from M6 to M9—3 months with the wristband and Fibrepik App in addition to the standard of care.

To avoid disappointment and lack of investment in the study by the Delayed group, we chose to provide the solution to this group after the collection of the main objective. The fact that these fibromyalgia patients could not benefit from the proposed innovative solution but only continue their usual treatment would have led to many patients refusing to participate or withdrawing consent. Since fibromyalgia is a long-term chronic disease, the 3-month delay for the Delayed solution group to benefit from the solution seems to be a very short period and perfectly acceptable.

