### Relevant concomitant care permitted or prohibited during the trial {11d}

All drug treatments or complementary therapies already initiated before the start of the study may be continued but the patient must not have any substantial modification of treatment (change in analgesic class, introduction of a new treatment) during the trial participation. At the end of each week, the patient reports the treatments and complementary therapies taken in their home follow-up booklet.

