## Discussion

The aim of this multicenter, randomized, and controlled study is to demonstrate the effectiveness of the integrative approach based on endorphins stimulation and a coaching program for patient suffering from fibromyalgia. If the effectiveness of the solution is demonstrated, we will be able to respond to the demand of fibromyalgia patients for access to an effective non-medicinal treatment to improve their quality of life, and confirm the key recommendation for nociplastic pain, emitted by the EULAR: drug-free approach as first intention and multidisciplinary care [39]. The randomization is of type immediate intervention vs delayed intervention. The Delayed group is the control group that receives the solution after the evaluation of the primary endpoint at 3 months. During these first 3 months, this group receives standard care, so we compare the solution to standard care. The purpose of this methodology is to limit deception bias and facilitate inclusion.

It is recommended that patients use the wristband for a minimum of 3 sessions per day. One of the strengths of this protocol is the follow-up in real-time and for each patient of the realization of the sessions thanks to the extraction of the data from the wristband to the smartphone application. This allows the patient to know at any time of the day the number of sessions performed. This data also allows coaches to remotely monitor their patients’ compliance. In case of poor compliance, the coach can recommend to the patient to increase the frequency of use during a coaching session or by sending a notification to the patient's smartphone. This objectivized compliance with real data will allow us to carry out our per-protocol analysis with patients having completed at least 80% of days with two or more sessions per day.

One of the weaknesses of this protocol is that it is not double-blind, as most of the non-medication and multi-disciplinary clinical trial, as it is impossible to use a placebo arm. However, the primary endpoint and most of the secondary endpoints are patient self-reports.

In addition, patients are encouraged to complete their questionnaires and booklet directly on the eCRF at home, which makes these data independent of any clinician or coach judgment.

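### The per-protocol rule rests on wristband use, which before M3 exists only in the Immediate group, so a per-protocol comparison at M3 is not randomised and may be biased

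*Protocol article*

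**What the plan says.** The section on non-adherence and missing data ({20c}) makes intention-to-treat the basis of all analyses. It then adds that "a per-protocol analysis will be performed by keeping only patients who have been compliant with the treatment". A patient counts as compliant if "during the first 3 months of solution use, we observe at least 80% of days with two or more sessions per day", and the source is explicit: "This number of sessions is an extract of the wristband log file". The Discussion repeats the rule. Neither place gives a separate rule for the Delayed group or says which comparison the per-protocol set serves.

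The description of the Delayed group gives its first period as "from D0 to M3—3 months with the standard of care", and explains that "we chose to provide the solution to this group after the collection of the main objective". The participant timeline ({13}) places wristband delivery and first coaching for this group at three months. The primary endpoint ({12}) is FIQ response, a fall of 14% or more, from D0 to M3.

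**The concern.** A per-protocol comparison is useful only if the same rule can be applied to both arms over the period in which the outcome arises. Here it cannot. No Delayed patient can meet or fail a log-based criterion before M3, because there is no log.

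The rule then has two workable readings. In (a), Immediate non-adherers are removed and all Delayed patients stay. In (b), taken literally, Delayed patients are selected on their own first three months of use, M3 to M6, after their M3 FIQ was recorded. Both lose the balance that randomisation provided.

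The article itself suggests that use and response are linked. Patients adapt use to how their symptoms evolve, and the number of sessions may be revised with the coach ({6b}). At M1 and M2 the coach reviews perceived change and advises on frequency ({11a}). Patients who stop because of an adverse effect remain in follow-up ({11b}), and before M3 only Immediate patients can fail the rule that way. What is at stake is a secondary result that could be read as support for, or against, the solution when it partly reflects who was kept.

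**Working it through.** **1. Timing, side by side**

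| | D0 to M3 | M3 | M3 to M6 |
|---|---|---|---|
| Immediate | wristband, app, coaching | primary endpoint | wristband, app |
| Delayed | standard care, no wristband | primary endpoint, then wristband handed over | wristband, app, coaching |
| Log rule assessable | Immediate only | | Delayed for the first time |

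Under {20a}, the M3 criteria are analysed once every patient has made the M3 visit. Inclusions ended on 1 April 2022 (Trial status), so the last M3 visit falls around 1 July 2022 and the last M6 visit around 1 October 2022. At the first analysis stage the Delayed logs for M3 to M6 are therefore incomplete, and reading (b) cannot be carried out in full. That leaves (a), unless the per-protocol analysis is postponed.

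**2. The plan's own figure**

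Inputs from {14}: 50% against 25%, alpha 5%, power 90%. Two-sided, pooled variance under the null:

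n = [1.960 × √(2 × 0.375 × 0.625) + 1.282 × √(0.25 + 0.1875)]² / 0.25² = 76.7, so 77 per group.

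This reproduces the stated 77. It does not depend on the per-protocol rule; it supplies the 25% rate and group size used below.

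**3. Reading (a), selection by response**

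Assume no treatment effect. Let r be the true response rate, and cR and cN the proportions of responders and non-responders who meet the rule. The rate among those kept is

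r × cR / [r × cR + (1 − r) × cN].

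The values of cR and cN are assumptions; the article gives none.

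| r | cR | cN | Calculation | Rate kept | Shift from r |
|---|---|---|---|---|---|
| 25% | 70% | 60% | 0.175 / 0.625 | 28.0% | +3.0 points |
| 25% | 80% | 50% | 0.200 / 0.575 | 34.8% | +9.8 |
| 25% | 80% | 40% | 0.200 / 0.500 | 40.0% | +15.0 |
| 25% | 70% | 70% | 0.175 / 0.700 | 25.0% | 0 |
| 25% | 60% | 75% | 0.150 / 0.7125 | 21.1% | −3.9 |
| 50% | 80% | 50% | 0.400 / 0.650 | 61.5% | +11.5 |

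The fourth row is the neutral case and the fifth the reverse case.

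**4. Reading (a), selection by prognosis**

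Assume no effect, 25% response overall, a share c of Immediate patients adhering, and adherers k times as likely to respond as non-adherers whatever the treatment. The adherers' rate is k × 0.25 / (c × k + 1 − c).

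- c = 80%, k = 1.5: 0.375 / 1.4 = 26.8%, or +1.8 points. With 62 adherers against 77 controls, the two-sided Fisher test rejects with probability 0.046.
- c = 50%, k = 3: 0.75 / 2 = 37.5%, or +12.5 points. With 38 adherers against 77 controls, it rejects with probability 0.248.

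At the mild end there is no material inflation; at the other end the nominal 5% is about 25%.

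**5. Reading (b), controls selected after their endpoint**

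The formula of step 3, applied to Delayed patients at r = 25%:

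- cR 50%, cN 75%: 0.125 / 0.6875 = 18.2%
- cR 60%, cN 75%: 21.1%
- cR 75%, cN 60%: 0.1875 / 0.6375 = 29.4%
- cR 80%, cN 60%: 0.200 / 0.650 = 30.8%

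The control rate moves either way. It stays at 25% only if later use is unrelated to M3 response. Nor need it cancel the shift in the Immediate group: there, use accompanies the response; in the Delayed group it follows it.

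**The case against.** The strongest reply is that little depends on this analysis. Intention-to-treat is primary, the Fisher test and sample size are untouched, and selection on adherence limits any per-protocol analysis. That stands, and it sets the weight of the point. It does not remove it: the asymmetry between arms is specific to this design and follows from a rule the article states.

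A second reply is that an unseen analysis plan may say how Delayed patients enter the set. It may. But the published criterion is specific, and a log-based criterion cannot be made symmetric before M3 by adding detail.

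A third is that the rule makes sense for the Delayed group's paired M3-to-M6 comparison ({20a}), where use falls inside the period assessed. This is right, and the log-based rule can be kept there.

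Some stronger readings are tempting and not supported:

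- A reader might infer that the per-protocol result will almost surely look better than intention-to-treat. The direction depends on assumed adherence. Patients may add sessions, and coaches prompt poor compliers, so higher use among non-responders is possible.
- A reader might infer that the compliance cut-off contradicts the Discussion's "It is recommended that patients use the wristband for a minimum of 3 sessions per day". The lowest mean that passes is 0.8 × 2 = 1.6 sessions a day, with none on the other days. That is a floor, not an expected average, and a cut-off below recommended use is not a contradiction.
- A reader might infer that the Discussion presents the per-protocol analysis as a strength. The strength it names is real-time follow-up of sessions; the analysis is something those data permit.
- A reader might infer that a prohibited treatment change is the only deviation possible in both arms before M3. Eligibility violations and M3 visits outside the window can also occur in both.

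**Conclusion.** The point holds for the M3 between-group comparison. As written, the rule yields a contrast between selected Immediate patients and either unselected controls or controls selected on later behaviour, and neither is a randomised comparison.

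The documents do not fix the size or direction of the bias. Under the stated assumptions (no effect, 25% response, 70-80% of responders and 40-60% of non-responders compliant), the Immediate per-protocol rate is 28-40% against a true 25%. With adherence unrelated to response the bias is nil, and with the opposite relation it works against the solution. Severity is modest: this is a supplementary analysis, and the primary conclusion does not rest on it.

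**What to change.** For the M3 between-group comparison, define the per-protocol set only by deviations that can be observed in both arms by M3. The article already supplies candidates: an eligibility violation ({10}), a breach of the condition that "the patient must not have any substantial modification of treatment" ({11d}), or an M3 visit outside the window of one week early to two weeks late (Table 1). Some of these arise after randomisation, so the result should still be read as supportive only.

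Report response by wristband use within the Immediate group as descriptive. Keep the log-based rule, if wanted, for within-group analyses such as the Delayed M3-to-M6 comparison.

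Optionally, add a supplementary complier-average estimate with randomised group as instrument: the intention-to-treat difference divided by the proportion of Immediate patients who adhere, Delayed use before M3 being zero by design. State its limits. Patients know their group, coaching also reaches low users and FIQ is self-reported, so the exclusion restriction is doubtful. Using session counts as the exposure would add a dose-response assumption. The interval will be wider than for intention-to-treat.

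The cost is a few sentences of analysis-plan wording before the database freeze and, if the option is taken, one extra model. All the data are already being collected.
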